#### Patient allocation

Patients will be allocated to a control group (i.e., usual care) or the intervention group using an “On-Off” group assignment method (Figure 1) This method has been previously used in quality improvement studies [19-21], and meets study design quality criteria to permit inclusion in the Cochrane Collaborations’ Effective Practice and Organization of Care (EPOC) systematic reviews [22]. Conceptually, eligible PCN patients will enter a “recruitment pool” then allocated to the intervention or control group in sequential clusters. This recruitment cluster will be filled through a number of strategies, with an aim of 50 participants at a time. The first strategy will be through active identification of newly diagnosed patients on each of the PCN’s diabetes patient registry. It is recognized that not all newly diagnosed patients will be immediately identified through this registry and therefore as a second strategy, we will recruit newly diagnosed patients through other PCN referral registries (i.e., patients attending basic diabetes education classes). Newly diagnosed patients will be given priority entry into the intervention since they may be more likely to adopt new behaviours versus those having diabetes for a longer period of time.

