#### Program delivery training for exercise specialists

One Exercise Specialist (i.e., certified by the Canadian Society of Exercise Physiology) will administer the intervention at each PCN. A full day workshop for all specialist detailing the delivery of the HEALD intervention will be organized and led by [name] (developer of the HEALD intervention). [name] will also meet with each Exercise Specialist at each PCN to review the HEALD materials prior to the delivery of the first HEALD group session. Study manuals that cover all aspects of the HEALD intervention will be provided at the training workshop.

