### Analytic strategy

All statistical tests will be two-sided with a level of significance set at 0.05 to evaluate the effectiveness of the intervention. Baseline comparisons will be performed using univariate analysis of variance (ANOVA) for continuous variables and chi-square analyses for categorical variables. The main analysis of our study is to compare the physical activity of the HEALD-PCN intervention (On) group participants to the usual care (Off) group, from baseline to 6 months as our primary assessment time-point. Employing the intention-to-treat (ITT) approach, we will also assess differences in group changes from: (1) baseline to 3 months, (2) baseline to 6 months, (3) and 3 months to 6 months using generalized linear mixed-model analysis (GLMM). GLMM uses all available data and provide a valid analysis when data are missing at random. The models will use baseline values for each outcome variable as a covariate to reduce the residual standard error and account for regression to the mean. Potential confounding variables (i.e., age, sex and BMI) will be included as covariates in the models. All data will be analyzed using Statistical Package for the Social Sciences v.20, SPSS Inc., Chicago Illinois, USA and Stata SE 10.1, StatCorp, College Station, Texas, USA.

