Based on the study’s design, we will account for 2 measurement points for the main dependent outcome (i.e., physical activity behavior at 6 months) across the study groups. In a 2 time-point, 2 group, repeated measures design with an a priori fixed and random effects model set to detect a moderate effect size (f = 0.25) while assuming a modest correlation (r = 0.5), the required sample size is 86 participants per group (power = 0.90; alpha = 0.05) [48-50]. Sample size was also estimated at 75 participants per group for average steps per day assuming an increase of 1,750 steps; that is, 8,250 versus 6,500 ± 3,300 steps/day for the intervention group over the control respectively (power = 0.90; alpha = 0.05). Our sample size estimate for our primary outcome is also sufficiently powered to detect a clinically meaningful difference between the groups of 0.5% for HbA1c assuming a baseline HbA1c of 7.2 ± 1.2%. This baseline estimation of HbA1c was derived from data provided by the Alberta Diabetes Surveillance System [17]. Given the length of follow-up period, we conservatively estimate that the rate of attrition during the intervention could reach 20% [51], and so our sample size was increased to 110 per group to account for the possibility of loss to follow-up.

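### Patients are allocated in sequential clusters of about 50, but the sample size assumes independent patients and no block term is named in the model, so the 0.90 power and 0.05 error rate hold only without within-cluster correlation

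*Protocol article*

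**What the plan says.** - **Allocation.** Under Patient allocation, eligible patients enter a pool and are "then allocated to the intervention or control group in sequential clusters". The size is also given: "This recruitment cluster will be filled through a number of strategies, with an aim of 50 participants at a time". The abstract and the text after Figure 1 add that blocks last two months.
- **Delivery.** There are four PCNs. One Exercise Specialist "will administer the intervention at each PCN", and group meetings take place in weeks 1, 2, 13 and 14.
- **Sample size (Analytic strategy).** The main calculation is "set to detect a moderate effect size (f = 0.25) while assuming a modest correlation (r = 0.5"), leading to "the required sample size is 86 participants per group (power = 0.90; alpha = 0.05"). A second calculation, for steps, uses "8,250 versus 6,500 ± 3,300 steps/day for the intervention group over the control respectively" and gives 75 per group. The number is then raised to 110 per group for 20% attrition. No ICC, design effect or number of blocks appears.
- **Analysis (Analytic strategy).** A generalized linear mixed model uses the baseline value as a covariate, and "Potential confounding variables (i.e., age, sex and BMI) will be included as covariates in the models". "All statistical tests will be two-sided with a level of significance set at 0.05". No allocation block is named. The limitations listed in the Discussion cover non-randomisation and the vague definition of usual care, but not clustering.

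**The concern.** The unit switched between arms is a group of patients recruited in the same two months, not a patient. Patients in one block share a season, and within a PCN those in an On block also share a specialist, a facility and group sessions. The primary outcome is physical activity, largely walking, so a shared seasonal effect is plausible. On and Off blocks also fall in different calendar periods, so variation between blocks goes directly into the treatment contrast.

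An analysis that treats patients as independent then gives a standard error that is too small. Two stated figures are at stake: the 0.05 error rate of the primary test and the 0.90 power that justifies the trial's size.

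**Working it through.** **1. Reproduce the plan's figures.** For two groups d = 2f = 2 × 0.25 = 0.5.

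- Normal quantiles: n = 2(1.960 + 1.282)² / 0.5² = 84.1, so 85.
- Exact t-test: 85 per group gives power 0.8999 and 86 gives 0.903, so 86. This is the stated figure.
- A change score at r = 0.5 has SD = √(2(1 − 0.5)) = 1 times the outcome SD, so it needs the same n.
- Steps: n = 2(1.960 + 1.282)² × 3,300² / 1,750² = 74.7, so 75, as stated.
- Attrition: 86 / 0.8 = 107.5, so 108, against 110 planned. The increase is used up by attrition.

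Both sample sizes are correct for independent patients and contain no allowance for clustering.

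**2. Cluster structure.** Completers: 110 × 0.8 = 88 per group. Recruitment: 220 / 50 = 4.4, so about four blocks, two per arm, if 50 is the total across PCNs. Two readings of the cluster follow:

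- calendar block: 4 clusters of 2 × 88 / 4 = 44;
- PCN-by-block cell: 4 × 4 = 16 clusters of 44 / 4 = 11.

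**3. Formulas.** The ICC is assumed (0.01 to 0.05), with equal cluster sizes and the same ICC in both arms.

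- Design effect DE = 1 + (m − 1) × ICC.
- Type I error if clustering is ignored = 2[1 − Φ(1.96 / √DE)].
- Power uses 88 / DE effective patients per group. With the planned baseline adjustment at r = 0.5 the residual SD is √(1 − 0.5²) = 0.866.

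| Cluster | ICC | DE | Type I error if ignored | Power, unadjusted | Power, baseline-adjusted |
|---|---|---|---|---|---|
| Cell (16 of 11), 14 df | 0.01 | 1.10 | 0.06 | 0.84 | 0.92 |
| | 0.02 | 1.20 | 0.07 | 0.80 | 0.90 |
| | 0.05 | 1.50 | 0.11 | 0.71 | 0.83 |
| Block (4 of 44), normal quantiles | 0.01 | 1.43 | 0.10 | 0.79 | 0.89 |
| | 0.02 | 1.86 | 0.15 | 0.68 | 0.80 |
| | 0.05 | 3.15 | 0.27 | 0.46 | 0.58 |

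Simulating a patient-level t-test with two blocks of 44 per arm gave type I error of 0.050, 0.102, 0.149 and 0.274 at ICC 0, 0.01, 0.02 and 0.05, in line with the formula.

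**4. Degrees of freedom.** Four blocks leave 4 − 2 = 2 df. A block-level test with baseline adjustment then has power of about 0.54 even at ICC 0, and 0.42 / 0.35 / 0.24 at ICC 0.01 / 0.02 / 0.05. The value at ICC 0 shows that much of this loss comes from the small number of blocks rather than from the correlation.

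**5. Slack in the plan.** Baseline-adjusted, 65 per group give power 0.904, so 88 completers absorb a design effect of 88 / 65 = 1.35 on large-sample degrees of freedom. For blocks of 44 that is an ICC of 0.35 / 43 = 0.008. For cells of 11 it is 0.35 / 10 = 0.035, or about 0.02 once 14 df are used, as the table shows.

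**6. Does omitting PCN inflate the error rate?** The Qualitative follow-up section samples from both study groups at every PCN, so PCN is crossed with arm. In 20,000 simulated trials with four PCNs, 22 patients per arm in each and variance shared at PCN level only, a patient-level t-test had type I error of 0.049 / 0.047 / 0.044 at ICC 0.01 / 0.02 / 0.05. There is no inflation.

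**The case against.** Several points limit the concern, and most of them stand.

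- **A reader might infer that 0.90 power is simply not delivered.** The figures do not support that. If cells are the clusters and the planned baseline adjustment is used, power is still 0.90 or above at ICC 0.01 and 0.02. The slack does not, however, protect the type I error.
- **A reader might infer that the missing PCN term raises the false-positive rate.** It does not, as step 6 shows. Leaving PCN out costs some precision; only variation between blocks or between PCN-by-block cells inflates the error.
- **A reader might infer that the model certainly ignores clustering.** The article names a mixed model and, in the sample-size paragraph, a fixed and random effects model, without listing the random effects. A fuller plan may include a block term. In the article, though, the random effects are tied to the two-time-point, two-group repeated-measures layout, and the power calculation remains one for independent patients.
- **The ICC is assumed.** Group contact is limited to four weeks of an otherwise self-monitored programme, and only in the intervention arm. A small ICC is therefore possible, and one common value for both arms is a simplification. Shared season and site still make exactly zero hard to defend.
- **The cluster structure is not fully documented.** The text does not say whether 50 is per PCN or in total, or whether PCNs switch together, and the flow diagram is not available here. The four-block figures rest on the total reading. If 50 is per PCN, one round could hold 4 × 50 = 200 of the 220 patients, leaving perhaps one block per arm, and period could then not be separated from arm.

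**Conclusion.** The concern holds in conditional form. The sample sizes of 86 and 75 are those for individually allocated, independent patients, while the article describes allocation by cluster. The named model terms do not make up the difference. The 0.05 error rate holds for a patient-level test only if within-cluster correlation is zero, and the 0.90 power is not assured.

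The size depends on which unit carries the correlation. With cells it is modest: type I error of 0.06 to 0.11 if ignored, and baseline-adjusted power of 0.92 down to 0.83. With whole calendar blocks it is serious: type I error of 0.10 to 0.27, and power of 0.89 down to 0.58 before the 2 df are taken into account. These ranges assume an ICC of 0.01 to 0.05, r = 0.5, 88 completers per group, equal clusters and, for blocks, 50 as the total across PCNs. The sample-size half is firm. The model half is less certain, because the random effects are not spelled out.

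**What to change.** **Analytic strategy, model paragraph.**
- Add a random effect for allocation cluster (PCN-by-block) beside the patient-level term, with a small-sample degrees-of-freedom method such as Satterthwaite.
- Include PCN as a fixed effect, for precision.
- A PCN-by-block effect does not absorb variation shared by a whole calendar block. So add a calendar term, such as season of assessment, where the On and Off blocks allow it. State as a limitation that an effect common to a whole block cannot be fully separated from arm with so few blocks.

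**Analytic strategy, sample-size paragraph.**
- Give the expected number and size of blocks, and say whether 50 is per PCN or in total.
- Say that 86 and 75 assume independent patients.
- Restate power for 110 per group under the baseline-adjusted analysis over an ICC range of 0.01 to 0.05, noting that 88 completers absorb a design effect of about 1.35.

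**Cost.** No extra patients. Confidence intervals widen, more so if calendar-block variation matters, and the stated power becomes less favourable.

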## Discussion and conclusions

We have described the rationale and design of a trial that is pragmatic and applicable to examine the effectiveness and efficiency of a population-based strategy for two important components of chronic disease management among adults with T2DM. The HEALD-PCN intervention is a relevant approach to diabetes management, although some might argue that a self-management study for T2DM is not a novel intervention and that there is sufficient evidence for clinical improvements among this population after participating in an self-management interventions - we would agree. What is novel about this study is the implementation of the program in a “real world” setting, and by expanding the typical inter-disciplinary nature of the “diabetes team”; that is, participants will be recruited from primary care clinics in different areas of Alberta and Exercise Specialists who are now becoming more a part of the primary care disease management team, will deliver the program in routine care as it might be offered if not part of a research study. Moreover, we have established partnerships between a model for health care delivery (i.e., PCN) and a local resource (i.e., community recreation facility) that should support the achievement of some of the behavioural and clinical targets of diabetes management. This study will provide new information around clinical- and cost-effectiveness in the context of everyday primary care and thus it will significantly add to the current literature in health service delivery for diabetes self-management. The broader evaluation using the RE-AIM framework will produce timely and meaningful data for policy makers and health care providers interested in questions around the implementation and sustainability of this type of program. Having described the strengths of the current study, we also acknowledge the limitations of the HEALD-PCN study. First, although the design for the evaluation of HEALD-PCN is applicable from a health system delivery perspective (i.e., recruiting from patient registries to simulate regular patient invitations to PCN programs), it still remains a weaker design than a formal randomized controlled trial. Nevertheless, there is a need for pragmatic studies of this type, as questions related to the external validity should now take precedence over concerns of internal validity (i.e., the efficacy of the intervention has already been established) [18,52,53]. Second, as is often found in controlled quality improvement studies, the definition of usual care for the management of T2D is rather vague. For this study usual care may not reflect usual care in other primary care settings. To help answer any questions with respect to usual care in this setting, we will be collecting information from a system capacity perspective and from a patient perspective. As a result of the expected heterogeneity of usual care across the PCNs in this study, the generalizability of the findings will have to be contextualized to the individual PCNs if there are indeed substantial differences in what is deemed usual care. Nevertheless, the implementation of the study in four separate primary care settings allows for broader, comprehensive understanding with respect to issues of program effectiveness, applicability, feasibility and context. It is recognized that the currently available body of knowledge around this type of investigation handcuffs health policy makers and care providers when developing and initiating evidence-informed policies for new and existing health technologies and interventions [52-54].

In summary, healthy eating and active living remain cornerstones of T2DM management. Since the global prevalence of T2DM is expected to increase beyond previous estimates, best practices for promoting these self-management cornerstones at a population level are urgently needed. In addition to the T2DM population, the results of this study may provide valuable information relating to the implementation of other physical activity-based chronic disease prevention and management interventions.

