### Setting & population

This research will be carried out in four non-urban Primary Care Networks (PCNs) in Alberta, Canada. All PCNs are stand-alone physician-led corporations established to support family physicians through allied professionals, including: Chronic Disease Management Nurses, Registered Dietitian, Pharmacists, Health Promotion and Prevention Coordinators and Exercise Specialists. According to the Alberta Diabetes Surveillance System, the prevalence of diabetes in the province of Alberta was 5.5% in 2009 with approximately 20% over the age of 65 [17]. In the four participating PCNs, approximately 9,000 adult patients with diabetes are under the care of approximately 140 General Practitioners.

All PCNs in the current study provide some form of basic diabetes group education either through a group-based workshop or one-on-one counseling with a Registered Dietitian and/or Exercise Specialist by physician referral. It is recognized, however that these approaches to support lifestyle self-management are most likely insufficient to achieve and maintain lifestyle changes in the longer term. Thus, the HEALD program is intended to be an enhanced follow-up behavioral support program, prescribed for patients who have already received some form of basic diabetes self-management education. The HEALD-PCN evaluation will be over and above the baseline self-management education through a pragmatic controlled trial [18].

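### PCN is not named in the planned outcome model, although the comparison is non-randomised across four PCNs whose usual care is expected to differ

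*Protocol article*

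**What the plan says.** Setting & population: "This research will be carried out in four non-urban Primary Care Networks (PCNs) in Alberta, Canada". On the background service there: "All PCNs in the current study provide some form of basic diabetes group education either through a group-based workshop or one-on-one counseling". The article does not say which PCN offers which form.

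Patient allocation: patients go to the On or Off group in sequential two-month clusters, without randomisation. On filling them: "This recruitment cluster will be filled through a number of strategies, with an aim of 50 participants at a time". The text does not say how places divide among the PCNs, or whether the target of 50 is overall or per PCN.

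Analytic strategy: a generalized linear mixed model is planned. "The models will use baseline values for each outcome variable as a covariate", and "Potential confounding variables (i.e., age, sex and BMI) will be included as covariates in the models". The random effects are not identified. The sample-size paragraph mentions fixed and random effects for a two-group, two-time-point design, without a grouping unit.

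Discussion and conclusions: usual care is expected to be heterogeneous across PCNs. If the differences turn out to be substantial, "the generalizability of the findings will have to be contextualized to the individual PCNs".

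**The concern.** Without randomisation, the balance between groups rests on how the clusters happen to fill and on what the model adjusts for. The authors themselves identify PCN as a source of variation in the comparator. Delivery also varies with PCN, since one Exercise Specialist runs the programme at each. A characteristic that may relate both to group membership and to outcome belongs in the adjustment set, and the confounder list is worded as complete and omits it.

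If one PCN supplies a larger share of the On group than of the Off group, and its patients would do better or worse at 6 months whatever their group, part of that local difference is counted as programme effect. Baseline adjustment absorbs some of any PCN difference already present at entry. It does not absorb differences that arise during follow-up because local usual care differs.

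**Working it through.** **The plan's own figures (Analytic strategy).** Two-sided alpha 0.05, power 0.90, difference 8,250 − 6,500 = 1,750 steps/day, SD 3,300:

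n per group = 2 × (1.960 + 1.282)² × (3,300 / 1,750)² ≈ 2 × 10.51 × 3.556 ≈ 74.7, so 75, as stated. For f = 0.25 (d = 0.5 with two groups) a two-sample t calculation gives 85.03, so 86, as stated. With 20% attrition, 86 / 0.80 = 107.5, so 108; the plan uses 110, leaving 110 × 0.80 = 88 completers per group. None of these figures has a PCN input.

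**Bias from leaving PCN out.** For one PCN against the rest:

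bias = (its share of On − its share of Off) × (gap in mean 6-month outcome between PCNs, given the other covariates)

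The article gives neither factor, so both are assumed. Results in steps/day:

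| Gap between PCNs | 0 points | 5 points | 10 points | 20 points | 30 points |
|---|---|---|---|---|---|
| 500 | 0 | 25 | 50 | 100 | 150 |
| 1,000 | 0 | 50 | 100 | 200 | 300 |
| 1,750 | 0 | 87.5 | 175 | 350 | 525 |

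- Middle row, 10 to 30 points: 100 / 1,750 = 5.7% to 300 / 1,750 = 17.1% of the planned effect.
- Whole grid, excluding equal shares: 25 / 1,750 = 1.4% to 525 / 1,750 = 30%.
- Standard error of the unadjusted contrast with 88 completers per group: 3,300 × √(2/88) = 497 steps. The middle row from 10 to 30 points is therefore 0.20 to 0.60 standard errors.

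**Can unequal shares be ruled out?** Not from the text. If the clusters of 50 combine PCNs, 220 / 50 = 4.4, so only four or five clusters form the whole study. That is too few to count on the PCN mix evening out between groups.

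**Effect of adding PCN on sample size.** If PCN explained 1% to 10% of the variance in steps (assumed), the SD becomes 3,300 × √0.99 to 3,300 × √0.90, and n per group falls from 75 to between 74 and 68. The term does not raise the sample size.

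**Precision of PCN-specific differences.** Assuming equal PCN sizes, 88 / 4 = 22 completers per group per PCN:

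- 95% confidence interval half-width = 2.018 × 3,300 × √(2/22) ≈ 2,010 steps, wider than the planned effect.
- Power for 1,750 steps within one PCN is about 0.40. With 27 per group (110 / 4, rounded down, no attrition) it is about 0.48, and the half-width is about 1,800 steps.

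**The case against.** Several points on the other side stand.

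- A reader might infer that the plan promises a PCN-by-PCN effect estimate and fails to deliver it. It does not: the sentence in the Discussion is a conditional remark about generalizability.
- A reader might also infer that no PCN-level reading is possible. Implementation evaluation plans to document usual care and organisational factors and to compare impact across settings. Qualitative follow-up samples interviews by study group at each PCN. A by-PCN summary of outcomes also needs no model term.
- Bias is not shown. It needs unequal PCN shares, which the article neither states nor excludes. With equal shares, varying usual care makes the pooled effect an average over PCNs, not a biased one. The interview sampling presupposes participants from both groups at every PCN, so the documents do not support reading PCN and group as inseparable.
- Basic diabetes education is an entry criterion for everyone, and the Exercise Specialists share a workshop and manuals. Both reduce the differences between PCNs.
- The random effects are unidentified, and the full protocol or analysis plan, which is not shown, may include PCN.

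The last point does not dispose of the matter. The article does not leave the adjustment set open: it gives a specific list, and PCN is not on it. The random effects it mentions are tied to a repeated-measures design, where a participant effect is the natural reading.

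**Conclusion.** The point holds as an avoidable weakness in the stated model. It does not show that the comparison is biased. PCN is absent from the covariates, strata and random effects named in the article, in a four-PCN non-randomised comparison with no stated balancing and a comparator that the authors expect to vary by PCN.

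The possible bias of 100 to 300 steps/day, in either direction, is illustrative. It rests wholly on the assumed 1,000-step gap and 10 to 30 point share differences, before any reduction through baseline adjustment. The change is worth making because it removes this source of confounding at almost no cost, whether or not the shares turn out to differ.

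**What to change.** In Analytic strategy, add PCN (four levels) as a fixed effect in every outcome model, beside the baseline value, age, sex and BMI. The group contrast is then formed within PCNs. State what random effects the mixed model contains.

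Report the On minus Off difference for each PCN with its 95% confidence interval, labelled descriptive, and say that these estimates will be imprecise and are not a basis for ranking or testing PCNs.

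Cost: three degrees of freedom in a model with 220 enrolled participants (about 176 completers). If the PCN-specific differences come from a group-by-PCN term, that supportive model uses three more. PCN is known for every participant, so no new data, no larger sample and no change to allocation are needed.
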